### Statistical analyses

Required sample size calculation (PS: Power and Sample Size Calculations version 3.0.43, Nashville, TN, USA) is based upon the change in SPPB. A change of 0.5 in SPPB score has been defined as minimally important and change of 1.0 as substantially important. With a standard deviation (SD) of 2.0 for SPPB, a type I error rate of 5%, a power of 80%, and a drop-out rate of 25%, we will need approximately 80 patients in each group to detect a substantial change in SPPB, when the effects of protein supplementation are compared against no additional supplementation or isocaloric placebo with a Student’s t-test independently. Multiple comparison will be performed by Dunnett’s test [36]. The final sample size may differ slightly from this figure, because we will recruit participants from the entire 75 years and older population living in Porvoo, Finland, and the aim is to include as many as possible from those answering the postal questionnaire.

The statistical analyses will be performed by PASW statistics 18.0.3 (SPSS Inc. Chicago, IL, USA). In the baseline findings, for the continuous variables, descriptive values will be expressed by means with SD and medians with range. For the variables with a normal (Gaussian) distribution, statistical comparisons between the groups will be made by using an analysis of variance test. If the variables have a non-normal distribution or ordinal level, statistical comparison between groups will be performed with an independent samples Kruskal-Wallis test. Measures with a discrete distribution will be expressed as percentages (%) and analyzed by X^2^ or Fisher’s exact test when appropriate.

The results will be analyzed according to intention to treat. For the most important outcome parameters estimation of confidence interval (95%) will be used in addition to testing.

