**Methods/Design:**

During 2012 the entire 75 and older population (N = 3,275) living in Porvoo, Finland was contacted via a postal questionnaire. Persons at risk of sarcopenia are screened with hand grip strength and gait speed. Poorly performing persons are further examined by segmental bioimpendance spectroscopy to determine their skeletal muscle index. Sarcopenic patients (target N = 250) will be enrolled in a 12-month randomized controlled trial with three arms: 1) no supplementation, 2) protein supplementation (20 grams twice a day), and 3) isocaloric placebo. All the participants will receive instructions on simple home-based exercises, dietary protein, and vitamin D supplementation (20 μg/d). The recruitment of patients will be completed during 2013. The primary endpoint of the trial is the change in short physical performance battery score and percentage of patients maintaining or improving their physical performance. Secondary endpoints will be, among other things, changes in muscle functions, nutritional status, body composition, cognition, quality of life, use of health care services, falls, and mortality. The assessment times will be 0, 6, 12 and 24 months.

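### The stated 80% power belongs to unadjusted t-tests; under the planned Dunnett test it is about 69% to 71% per comparison, and the drop-out allowance is also miscalculated

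*Protocol article*

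**What the plan says.** All the inputs stand in the first paragraph of Statistical analyses in the protocol article.

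- **Effect:** the trial is sized on the "change of 1.0 as substantially important". A smaller change of 0.5 is called minimally important but is not the sizing target.
- **Variability:** "With a standard deviation (SD) of 2.0 for SPPB".
- **Error rate:** "a type I error rate of 5" per cent.
- **Power, losses and resulting number:** "a power of 80%, and a drop-out rate of 25%, we will need approximately 80 patients in each group to detect a substantial change".
- **Test behind the figure:** Student's t-test, protein against each of the two controls independently.
- **Test for the analysis:** "Multiple comparison will be performed by Dunnett’s test".

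The same paragraph allows the final number to differ slightly and aims to recruit as many eligible people as possible. The abstract gives an overall target of 250. Under Study procedures, the randomisation list has 300 slots, 100 per arm.

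**The concern.** Two steps in the paragraph do not fit together.

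1. A sample size is inflated for loss by dividing by the retained fraction, not by multiplying by one plus the loss. The figure of 80 looks like the product of the second method.
2. The 80% is computed at 5% for each comparison, while the named analysis spreads 5% over two comparisons that share the protein arm. The paragraph does not carry the calculation through to that stricter threshold.

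At stake is how a non-significant result would be weighed. On the stated inputs, the chance of missing a true 1.0-point benefit in a given comparison is about 31% (100% − 69.4%), where the paragraph implies 20%.

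**Working it through.** **Inputs** (Statistical analyses): difference δ = 1.0, SD σ = 2.0, α = 0.05, power 0.80, drop-out 25%, equal arms. Two assumptions are mine: testing is two-sided (the article does not say), and 2.0 is the SD of the analysed change.

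**1. Reproducing the printed figure.**
n = 2σ²(z₀.₉₇₅ + z₀.₈₀)²/δ² = 2 × 4 × (1.960 + 0.842)² = 62.8, so 63 by the normal approximation. The exact t-test solution is 63.8, so 64 evaluable per group (power 80.1%).

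- 64 × 1.25 = 80, the printed figure.
- 64/0.75 = 85.3, so 86, the number that leaves 64 after a 25% loss.

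A one-sided calculation needs 50 evaluable, or 67 with the correct allowance and 63 with the mistaken one. It does not lead to 80, which supports the two-sided reading.

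**2. Unadjusted power.**
Evaluable per arm: 80 × 0.75 = 60. Noncentrality: (δ/σ)√(n/2) = 0.5 × √30 = 2.739. Power is 77.5% by the noncentral t, and 78.2% by the normal approximation, Φ(2.739 − 1.960).
At the target of 250: 250/3 × 0.75 = 62.5 evaluable per arm, and power is 79.2%.

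**3. Power under Dunnett's test.**
Two comparisons sharing one arm have correlation 0.5. With df = 3 × (60 − 1) = 177, the two-sided critical value at a familywise 5% is 2.230, about 2.7% per comparison.

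| Randomised | Evaluable per arm | Unadjusted | Dunnett, per comparison |
|---|---|---|---|
| 80 per arm | 60 | 77.5% | 69.4% |
| 250 in total | 62.5 | 79.2% | 71.4% |

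Hand check at 60: Φ(2.739 − 2.230) = Φ(0.509), about 69.5%.

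Difference detectable with 80% power under Dunnett at 60 per arm: (2.230 + 0.842) × 2.0 × √(2/60) = 1.12. At 62.5 per arm: (2.229 + 0.842) × 2.0 × √(2/62.5) = 1.10.

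For reference, 80% power per Dunnett comparison needs 76 evaluable per arm; 76/0.75 = 101.3, so 102 randomised per arm.

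**4. Which SD is 2.0?**
The outcome is the change in SPPB, but the SD is given for SPPB. If 2.0 is the SD of the score at each visit, and r is the baseline-to-follow-up correlation, the SD of the change is 2.0 × √(2(1 − r)). The article gives no r, so a range is shown, at 60 per arm:

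| r | SD of change | Dunnett power per comparison |
|---|---|---|
| 0.4 | 2.19 | 61% |
| 0.5 | 2.00 | 69% |
| 0.6 | 1.79 | 80% |
| 0.7 | 1.55 | 90% |

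The two readings coincide at r = 0.5.

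**The case against.** **The drop-out slip hardly matters.** The article says approximately 80, allows the number to move, and targets 250, where unadjusted power is 79.2%. This stands. Taken alone, the slip would be a minor correction.

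**The list could hold more patients.** If all 300 slots were filled, 75 per arm would be evaluable, giving 86% unadjusted and 79.8% under Dunnett. This is an upper bound only, since the stated target is 250.

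**The article is open about what its 80% refers to.** It names independent t-tests, then Dunnett. That is fair, and nothing is hidden. But the paragraph offers 80% as the trial's power and never gives a figure for the adjusted comparisons. This is a mismatch between two printed statements, not a detail left to an analysis plan.

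**Misreading of a null result is guarded against.** Confidence intervals are promised for the most important outcomes, and the Discussion warns that deaths and comorbidity may lower power. Both soften the consequence; neither corrects the figure.

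**Stronger readings that the article does not support.** A reader might quote the power to beat both controls, about 55% at 60 per arm if the benefit is 1.0 against each. The plan sets no such criterion, and on the same assumptions the power to win at least one comparison is 84%. Since the article powers each comparison separately, the per-comparison figure is the like-for-like one. A reader might also take 69% as certain; it depends on which SD the 2.0 is. Nor can baseline adjustment be counted on to restore 80%. The article's sample size paragraph names no such analysis, and at 60 per arm under Dunnett its power runs from about 77% to 94% for r from 0.4 to 0.7, depending on the meaning of the SD.

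**Conclusion.** The paragraph is wrong as written, in two ways of unequal weight. The drop-out allowance is miscalculated (80 where 86 is needed), which costs about 2.5 points of unadjusted power, or under one point at the target of 250. The material error is that the 80% does not belong to the named multiple-comparison test, under which power for 1.0 point is about 69% per comparison at 80 per arm and about 71% at 250.

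These figures assume two-sided testing and an SD of 2.0 for the change. With one-sided tests, power at 60 per arm would be 86% unadjusted and 79% under Dunnett, but the article does not specify them. If 2.0 is the SD of the score, a correlation of about 0.6 or more would bring Dunnett power to roughly 80% or above, so it cannot be said outright that the trial is underpowered. What can be said is that the stated inputs and the stated test do not yield the stated power. The treatment estimate is not biased and the type I error is not inflated.

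**What to change.** Rewrite the sample size paragraph so that it:

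- gives 60 evaluable per arm at 80 randomised, and 62.5 at the target of 250;
- gives about 69% to 71% power per Dunnett-adjusted comparison for a 1.0-point difference, and a detectable difference of about 1.1 at 80% power;
- states that testing is two-sided;
- corrects the drop-out allowance to division by 0.75, so that 64 evaluable corresponds to 86 randomised for the unadjusted test;
- says whether 2.0 is the SD of the score or of its change and, if of the score, gives power over a stated range of correlations.

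If a gain from baseline adjustment is to be claimed, show it only as a range over stated correlations.

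The cost is one reworded paragraph and a less favourable stated power. No extra patients and no change in conduct are needed.

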### Outcome measurements

The examinations are performed at 0, 6 and 12 months. In addition to this, follow-up data are also collected from registries at 24 months.

Primary outcome measures are:

1. The 6- and 12-month changes in physical performance according to mean SPPB [21] and CSPPS [22,23] scores

2. Changes in muscle functions according to hand grip strength [17], gait speed [18], balance [19], chair stand test [24], two-minute step test [25]

Secondary outcome measures are:

1. Compliance to supplementation and home based exercises

2. Patient reported benefits and adverse effects

3. Changes in nutrition according to MNA [26], diet quality questionnaire [27], and dietary records [28]

4. Changes in body composition according to BMI and segmental BIS measurements [6,19]

5. Changes in cognition according to MMSE [20], verbal fluency [29,30] and clock drawing test [31], and CDR sum of boxes [35]

6. Changes in HrQOL measures according to SF-36 [32] and 15D [33]

7. Number of falls

8. Serum and plasma markers of inflammation, anabolism, glycemic control and renal function

9. Use of health care (number of hospitalization/follow-up time) and social services (number of institutionalization/follow-up time) during a 24 month follow-up

10. Mortality during a 24 month follow-up

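### Only unadjusted tests are named for the change in SPPB although baseline SPPB is measured; adjusting for it adds precision, by an amount that depends on a correlation the article does not give

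*Protocol article*

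**What the plan says.** Under Outcome measurements, the first primary outcome is "The 6- and 12-month changes in physical performance according to mean SPPB", with CSPPS alongside it. Under Statistical analyses, the sample size "is based upon the change in SPPB". The importance thresholds are given as follows: "A change of 0.5 in SPPB score has been defined as minimally important and change of 1.0 as substantially important". The spread enters as "With a standard deviation (SD) of 2.0 for SPPB", and protein is to be "compared against no additional supplementation or isocaloric placebo with a Student’s t-test independently". The next sentence assigns the multiple comparison to Dunnett's test.

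The following paragraph begins with the baseline findings. It names analysis of variance for normal variables and then states: "If the variables have a non-normal distribution or ordinal level, statistical comparison between groups will be performed with an independent samples Kruskal-Wallis test". The section closes with intention to treat and 95% confidence intervals for the most important outcomes.

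No test or model that uses a baseline covariate is named for any outcome. Table 1 schedules SPPB at baseline, 6 and 12 months, so the covariate is collected. The randomisation procedure described after Table 1 does not stratify on it.

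**The concern.** A change score subtracts the whole baseline value, which fixes the baseline slope at 1. When the correlation between baseline and follow-up is below 1, that is more correction than the data call for, and the contrast is noisier than it need be. A model that estimates the slope has equal or smaller residual variance.

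Two things are at stake. The first is precision: under the Dunnett test that the article names, the planned numbers give less than 80% power per comparison if SD 2.0 applies to the change (shown below). The second is chance imbalance: without stratification on SPPB, a baseline difference between arms carries into the change-score contrast through regression to the mean.

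**Working it through.** **Inputs from Statistical analyses:** difference 1.0, SD 2.0, type I error 5% (two-sided reproduces the plan's figure), power 80%, drop-out 25%, about 80 per group. **Assumptions, not in the document:** the correlation r between baseline and follow-up SPPB, and equal variance at both visits.

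**1. The plan's own figure.** The normal approximation gives n = 2(1.960 + 0.842)² × 2.0² / 1.0² = 62.8, so 63 per group; the exact t calculation gives 64. Then 64 × 1.25 = 80. The stated figure is therefore an unadjusted two-sided t-test, inflated by multiplication, with no Dunnett correction.

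**2. Power at the expected completers.** 80 × 0.75 = 60 per arm. The noncentrality is 1.0 / (2.0 × √(2/60)) = 2.739. Power is 77.5% with a t-test. With the Dunnett two-sided critical value for two comparisons (2.23 at about 177 degrees of freedom) it is 69.4% per comparison.

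**3. Variance ratio.** Let σ be the SD of the score. The change has variance 2σ²(1 − r), and the baseline-adjusted residual has variance σ²(1 − r²). The ratio is (1 − r)(1 + r) / [2(1 − r)] = (1 + r)/2. This is 0.75 at r = 0.5, 0.85 at 0.7 and 0.90 at 0.8.

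**4. Power per comparison if 2.0 is the SD of the change** (60 per arm, critical value 2.23). Adjusted SD = 2.0 × √((1 + r)/2).

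| r | adjusted SD | change score | adjusted |
|---|---|---|---|
| 0.5 | 1.732 | 69.4% | 82.4% |
| 0.6 | 1.789 | 69.4% | 79.7% |
| 0.7 | 1.844 | 69.4% | 77.0% |
| 0.8 | 1.897 | 69.4% | 74.4% |
| 0.9 | 1.949 | 69.4% | 71.9% |

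Power returns to 80% only if r is about 0.59 or lower. More than half of the gap from 69.4% to 80% closes only if r is below about 0.79.

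**5. Power per comparison if 2.0 is the SD of the score.** Change SD = 2.0 × √(2(1 − r)); adjusted SD = 2.0 × √(1 − r²).

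| r | change SD | adjusted SD | change score | adjusted |
|---|---|---|---|---|
| 0.3 | 2.366 | 1.908 | 53.5% | 73.9% |
| 0.5 | 2.000 | 1.732 | 69.4% | 82.4% |
| 0.6 | 1.789 | 1.600 | 79.7% | 88.3% |
| 0.7 | 1.549 | 1.428 | 90.3% | 94.5% |
| 0.8 | 1.265 | 1.200 | 98.2% | 99.0% |

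The two readings coincide at r = 0.5.

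**6. Chance imbalance.** At r = 0.5 both readings give a score SD of 2.0. The standard error of the baseline difference between two arms of 60 is 2.0 × √(2/60) = 0.365. An imbalance of one standard error moves the change-score contrast by (1 − 0.5) × 0.365 = 0.18 points, which is 0.18/0.5 = 36% of the change that the article calls minimally important.

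**The case against.** The strongest reply is about scope. This is a condensed article, and covariates are often left to an analysis plan. The t-test words stand in the sample-size sentence, and sizing on an unadjusted test does not bind the analysis. Dunnett contrasts can be formed from an adjusted model. All of this is right, and the article does not exclude adjustment. What remains is that the article does name its between-group tests, all of them unadjusted, and data already being collected allow a better one.

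Four stronger readings are tempting but not supported.

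- A reader might infer that Kruskal-Wallis is the primary test because SPPB is ordinal. That paragraph opens with baseline findings, while the outcome is defined through the mean SPPB and the section names Dunnett and confidence intervals. The scope of the rule is unclear, no more than that.
- A reader might infer that 2.0 is the SD of the score. The calculation is said to rest on the change, and the text does not settle which is meant.
- A reader might infer that adjustment recovers most of the lost power. That depends on r and on the SD reading. If 2.0 is the SD of the change, about 47% of the gap is recovered at r = 0.8: (74.4 − 69.4)/(80 − 69.4). If it is the SD of the score, there is no shortfall at r = 0.7.
- A reader might infer that the unadjusted result is biased. Under randomisation the change-score comparison is unbiased and keeps its type I error; chance imbalance is already in its standard error.

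**Conclusion.** The point holds as one of efficiency. The article names only unadjusted tests for the SPPB change, and a linear model with baseline SPPB as covariate would be at least as precise for any r below 1, apart from about one degree of freedom. The change score already uses the baseline value, so the gain is only the step to an estimated slope: 10% to 25% of the variance for r between 0.8 and 0.5. In power per comparison, that is 5 to 13 percentage points over the same range of r if 2.0 is the SD of the change. If it is the SD of the score, the gain is about 20 points at r = 0.3 and 4 at r = 0.7. These figures assume equal variances, 60 completers per arm and a true difference of 1.0.

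The n × 1.25 drop-out inflation and the absence of Dunnett from the sample size are separate points. Adjustment can offset their effect on power but does not correct them.

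**What to change.** - Analyse SPPB at 6 and 12 months (or its change) with a linear model on arm and baseline SPPB. Report the two protein-minus-control differences with Dunnett-adjusted 95% confidence intervals.
- Do the same for CSPPS and the other continuous outcomes, each with its own baseline value.
- State that the ANOVA/Kruskal-Wallis rule applies to baseline comparisons and does not replace these contrasts. Keep a rank-based version of the two contrasts as a sensitivity analysis.
- Say whether SD 2.0 is for the score or the change, and show power over a range of r.

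The cost is a few sentences of wording and about one degree of freedom; no new data or participants are needed. Recruitment was still under way at submission (Trial status), so the wording could be fixed before outcomes are compared by arm. The percentage maintaining or improving performance, which the abstract lists in the primary endpoint, is not covered by this linear model and needs its own stated analysis.

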## Discussion

This rigorous randomized controlled trial will test whether and to what extent protein supplementation is able to maintain physical performance in community dwelling older people with sarcopenia. In addition to protein supplementation, the systematic use of simple and evidence-based methods to maintain muscle health in old age including home-based exercise, vitamin D supplementation and protein rich foods are promoted among all participants. The intervention is pragmatic in nature, and is performed in close collaboration with the municipal health care services. Thus, if the intervention proves to be effective, it can be implemented easily.

The strength of this study is its pragmatic nature [37]. Thus, the findings should be applicable in real life. The target population is frail and vulnerable and, according to our previous studies, is at risk of adverse outcomes such as physical disability and poor quality of life and death. Thus, ceiling effect is not easily reached in the primary endpoint. Furthermore, the limited exclusion criteria and portable nature of all study procedures allow the inclusion those disabled older people that are otherwise often not included in clinical trials.

However, there are also potential limitations in this study. First, the population is old and frail with many comorbidities, and, thus, vulnerable to competing causes of complications and deaths. This may decrease the power of the study. The second challenge relates to a sufficient difference to be attained between the groups with our intervention because nutritional supplementation may diminish the intake of regular food. Furthermore, the long-term adherence of patients to single taste supplements and unsupervised home-based exercises is also a challenge to this study.

To our knowledge, this is the first large scale randomized controlled trial among community dwelling older people with sarcopenia that focuses on the effects of protein supplementation on physical performance and several aspects of muscle health, nutritional status, QoL, cognition and hospitalizations.

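### The tests named for SPPB change, run on observed data, leave later leavers out of the 12-month comparison; a repeated-measures model would use their 6-month data and reduce possible bias

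*Protocol article*

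**What the plan says.** All references are to the protocol article.

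- **Statistical analyses, principle.** "The results will be analyzed according to intention to treat". The section does not say how a missing SPPB or a death enters the analysis.
- **Statistical analyses, tests.** Student's t-test is named in the sample-size sentence, for protein against each of the two other arms. Dunnett's test is named for multiple comparison. The analysis of variance and Kruskal-Wallis sentences are introduced as concerning baseline findings. No other between-arm method is named for SPPB change.
- **Statistical analyses, sample size.** "With a standard deviation (SD) of 2.0 for SPPB", "a type I error rate of 5" per cent, 80% power and "a drop-out rate of 25" per cent give about 80 per group for a difference of 1.0. On importance: "A change of 0.5 in SPPB score has been defined as minimally important", and "change of 1.0 as substantially important".
- **Outcome measurements.** "The examinations are performed at 0, 6 and 12 months". The first primary outcome is the change in SPPB and in the continuous summary score at both 6 and 12 months.
- **Discussion.** The population is described as "vulnerable to competing causes of complications and deaths". The only consequence drawn is a possible loss of power.

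**The concern.** A t-test or Dunnett's test of observed 12-month change needs a 12-month SPPB. If a quarter of each arm is lost by then, about 20 of 80 randomised patients per arm do not enter that comparison. Those of them who were seen at month 6 have an SPPB that predicts where they were heading, but the 12-month test makes no use of it.

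SPPB measures physical decline, and in this population decline and death are likely reasons for loss. Those lost will therefore probably have done worse than those retained. If that holds equally in every arm, the difference between arms is not distorted. If it holds more strongly in one arm, or if more people leave one arm, the observed-data comparison can show an effect that is not there or hide one that is. More patients would not cure this, so treating loss only as a power problem misses the larger risk.

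**Working it through.** **1. Reproduce the sample size.** Inputs from Statistical analyses: difference 1.0, SD 2.0, type I error 5% (two-sided assumed), power 80%, drop-out 25%.

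n = 2 × (1.960 + 0.842)² × 2.0² / 1.0² = 62.8, so 63 per arm; the t-test version gives 64.
64 × 1.25 = 80, the stated figure. (Dividing by 0.75 would give 86.)

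The allowance treats those lost as giving no outcome. With 80 randomised and 25% lost, 80 × 0.75 = 60 per arm remain.

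**2. When observed-data change is biased.** Let d be the share lost in an arm, and g the mean change in those lost minus the mean change in those observed. The mean over all randomised is the observed mean + d × g, so

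bias of the difference (T minus C) = −(d_T × g_T − d_C × g_C).

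The article gives no d or g by arm, so every value below is assumed.

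| d_T, d_C | g_T, g_C | Bias (SPPB points) |
|---|---|---|
| 25%, 25% | −1, −1 (or −2, −2) | 0 |
| 25%, 25% | −1, 0 | 0.25 |
| 30%, 20% | −1, −1 | 0.30 − 0.20 = 0.10 |
| 30%, 20% | −2, −2 | 0.60 − 0.40 = 0.20 |
| 35%, 15% | −2, −2 | 0.70 − 0.30 = 0.40 |

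For one unadjusted two-sided t-test with 60 per arm, SE = 2.0 × √(2/60) = 0.365. A bias of 0.25 is 0.25/0.365 = 0.68 SE, and type I error rises from 5% to about 10.5%.

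**3. What the 6-month SPPB recovers.** Assumed: normal SPPB with SD 2; correlations 0.7 (baseline with 6 months), 0.7 (6 with 12 months) and 0.6 (baseline with 12 months); true effect 0; everyone seen at month 6; 25% lost afterwards in each arm. Loss is logistic in the SPPB change in one arm and random in the other. The slope is the log-odds of loss per point of decline.

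| Loss follows | Slope | Bias, observed 12-month change | Bias, likelihood using baseline and 6-month SPPB |
|---|---|---|---|
| 6-month change | 0.25 | 0.10 | 0.00 |
| 6-month change | 0.5 | 0.18 | 0.00 |
| 6-month change | 1 | 0.29 | 0.00 |
| 6-month change | 2 | 0.38 | 0.00 |
| 12-month change | 0.5 | 0.35 | 0.22 |

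By the formula in step 2, 0.10 to 0.38 corresponds to a one-sided gap of 0.10/0.25 = 0.4 to 0.38/0.25 = 1.5 points. The zeros are expected, because in those rows loss depends only on data the model sees. In the last row 0.22/0.35 = 63% of the bias remains.

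**The case against.** A reader might infer that the plan is a completers' analysis and so contradicts its own intention-to-treat statement. The article does not support that. Nothing restricts the analysis to completers, the same tests could follow imputation, and intention to treat may simply mean analysis by randomised arm. Allowing for drop-out in the sample size is ordinary planning and does not define an analysis set.

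A reader might also infer that the 6-month SPPB of later leavers goes unused. That is wrong: the 6-month change is itself a primary outcome, so these people inform that comparison. They are absent only from the 12-month one.

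The case for differential loss is limited. Protein and placebo participants take the same volume on the same schedule, so the burden of drinking cannot separate those two arms; it could bear only on protein against no supplementation. Stopping the drink need not end assessment, and the article stresses portable procedures and allows home visits at baseline. It reports no loss by arm.

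The sizes depend on the assumed strength of selection and on its acting in one arm only. The clean result for the model is also a product of the assumption that loss follows 6-month decline.

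Finally, missing-data rules are often left to a full protocol or analysis plan, neither of which is shown, so their absence here is not a fault. All of this stands. What remains is narrower: the article does name an analysis, and a better one is available from data already scheduled.

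**Conclusion.** The point holds as a worthwhile improvement, not as a proven error. Applied to observed data, the named tests omit at each visit whoever lacks an SPPB at that visit. With 25% loss expected in a population at risk of decline and death, the 12-month estimate can be biased if the rate of loss, or its link to decline, differs by arm. Under the assumptions in the working (25% lost per arm, loss following 6-month decline in one arm only), the bias is 0.10 to 0.38 points, or 20% to 76% of the 0.5 minimally important change (0.10/0.5 and 0.38/0.5). It is 0 when rate and pattern are the same in both arms, and the documents do not say which case applies. A reader should not conclude that the primary result will be biased, only that the named analysis offers no protection if loss is uneven.

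**What to change.** Make the primary SPPB analysis a mixed model for repeated measures:

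- outcome: SPPB at 6 and 12 months;
- terms: arm, visit, arm × visit, and baseline SPPB as covariate, with unstructured covariance;
- population: every randomised participant with any post-baseline SPPB, in the arm assigned;
- contrasts: protein against each control at each visit, keeping a Dunnett-type adjustment.

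Add one sensitivity analysis in which SPPB missing because of death or decline is given an unfavourable value, fixed before the arms are compared. State in the intention-to-treat sentence how missing SPPB values and deaths are handled.

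The cost is wording and analysis time. SPPB is already scheduled at all three visits, and recruitment was still under way at submission, so the rule could be set before outcomes are analysed.

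The downside is that the model assumes data are missing at random. It removes only part of the bias if loss depends on unobserved 12-month decline (about two thirds remained in the last row of the working), and it still omits anyone with no post-baseline SPPB. Hence the sensitivity analysis.
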